### Step 5: Development of a plan for implementation

Researchers pay attention in step 5 to important preconditions that ensure optimal implementation and adoption of the ‘Relieved Working’ study. Firstly, as managers and supervisors play a key role in successful implementing an intervention at worksites
[31], they are encouraged to actively participate in the intervention. Managers are also invited for a session with all participating companies to share ideas and learn about new innovations of technical control measures. Secondly, as time, place and costs are important factors to successfully adopt and implement the program
[32, 33], the three sessions are organized within the existing so-called “Toolbox Education system” in the Dutch construction industry. The toolbox education system consists of at least 10 obligatory health and safety training sessions for workers, which have to be organized by managers in the construction industry each year in order to obtain an official health and safety certificate. Thirdly, because the intervention is implemented across different companies, a protocol including an outline, time schedule, and communication between all stakeholders was developed to standardize the intervention.

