**Methods/Design:**

The intervention was developed according to the principles of the Intervention Mapping protocol, meaning that evidence from the literature was combined with information collected from stakeholders (e.g., construction workers, managers and researchers). The intervention aimed to integrate technical, behavioural and organizational factors. The intervention consists of two plenary meetings for all employers within the company, and individual visits at construction worksites, including specific intervention materials. Additionally, a demonstration session regarding control measures was organized for all managers. The effectiveness of the intervention will be evaluated in a cluster randomized controlled trial among eight construction companies, with measurements at baseline and follow-up. Outcome measures are personal respirable dust and quartz exposure by means of exposure assessment, and behavioural and organizational determinants which will be assessed by means of questionnaires. Additionally, a process evaluation will shed light on whether the intervention (does not) works, and, if so, the reasons for this.

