**Behavioral determinants**			
Awareness	Passive learning	Providing (written) information	Personal letter to workers with information regarding the exposure levels of the baseline measurement
	Modelling	Role modelling	Poster for managers and workers
	Stimulating communication	Discussion	Interactive group sessions to exchange constraints/facilitators of using technical control measures
Knowledge	Passive learning	Providing (written) information	Tailored factsheets for workers
			Occupational physician will attend first meeting to explain health-risks
	Active Learning	Discussion	Interactive presentations including documentary and PIMEX during sessions at the worksite
		Demonstration	
			Interactive group sessions at the worksite
			Discussion with labour inspector regarding the context of using technical control measures
			Tailored sessions for managers to demonstrate technical control measures
	Images	Providing verbal information/images	Video on long-term effects of occupational exposure
Risk perception	Scenario-based risk information	Recognizing invisible risks	Video on long-term consequences of occupational exposure
			Occupational physician will attend first meeting to explain health-risks
		Recognizing behaviour	Pimex videos^1^
Skills	Feedback	Feedback	Group discussions at the worksite
	Guided practice	Guidance sheet	Tailored factsheets
			Tailored sessions for managers to use technical control measures
	Modelling	Demonstration	PIMEX videos^1^

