Simultaneously with the worksite visits, a meeting is separately organized for the managers to gain more insight in the availability of technical control measures. This meeting consists of a demonstration of the newest available technical control measures, their innovations and their possibilities. As this session is held at the lab within the research institute, the managers have the possibility to practice with technical control measures and to discuss possible constraints related to functionality.

During the last plenary session at the company, managers and workers discuss, evaluate, and reconsider the goals and actions that are achieved. During an interactive presentation of the principal researcher, lessons learned and key-solutions to overcome the main constraints are discussed. The assignment with photos serves to open this discussion regarding the good and bad practices across different worksites. Additionally, a labour inspector joins this session to give practical information on their policy regarding quartz exposure.

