## Phase II: Evaluation of the intervention

### Step 6: Evaluation plan

#### Study design

The effectiveness of the intervention will be measured by performing a cluster randomized controlled trial (cluster RCT). Participants who have given informed consent are measured at baseline (T0), and will be measured after the intervention (T1). Workers at the worksite allocated to the intervention group receive the worksite intervention program during a six month period, while those allocated to the control group receive no intervention. The study protocol and measurements are not part of the judgement of the Central Committee of Research Involving Human Subjects, meaning no medical ethic approval is required for this study. The study has been executed according to the Dutch Data Protection Law.

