#### Randomization and blinding

In order to avoid intervention group contamination, to obtain maximal co-operation of managers and construction workers, and to enhance participants' compliance, cluster randomization at the level of the company is considered the best randomization strategy for this study. Randomization is performed by the principal researcher ([name]) using an electronic randomization tool (
http://www.randomizer.org) after the baseline measurement. Because the intervention takes place at the worksites, participating workers, managers, supervisors, as well as researchers/trainers cannot be blinded to the group assignment.

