##### Organizational factors

Managers of all participating companies receive a questionnaire in order to gain insight into the occupational safety and health policy
[22]. This questionnaire is based on the Occupational Health and Safety Assessment Series (OHSAS) norm for health and safety management, and specifically focuses on hazardous substances
[23]. The following themes were included: (i) the presence and compliance of work procedures and workplace instructions; (ii) the extent to which training and education is offered to employees; (iii) the presence of management support towards a proactive health and safety culture (e.g.., toolbox meetings on a fixed and regular schedule to stimulate discussion between managers and construction workers); and (iv) the method of communicating and providing feedback with equipment contractors to improve services.

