## Discussion

In this paper, the development of the ‘Relieved Working’ study and the design of its evaluation are described. This multidimensional intervention aims to establish an increase in the (proper) use of technical control measures by targeting both the workers’ behavior and organizational factors in order to significantly reduce occupational respirable dust and quartz exposure in the construction industry.

To our knowledge, this is the first study that will evaluate a multidimensional intervention in the construction industry tailored to both construction workers and managers. Since developing complex interventions, as in the present study, is a considerable challenge
[43], intervention mapping was used to design an intervention which is not only tailored to the needs of the target population, but also to the abilities and opportunities of managers and implementers. A strength in applying intervention mapping in this study was that quantitative (i.e., baseline study) and qualitative information of construction workers was systematically collected and combined with scientific literature to tailor the intervention to their needs. By also involving managers in the development, it eventuated that managers played an important role in the availability of technical control measures at all worksites. An additional informative session is therefore organized for all managers. Involving all stakeholders in the development of the intervention was another strength, as it provided insight into the practical strategies. For example, the intervention is incorporated within the existing ‘Toolbox Education System’ of the construction industry. Because this education system is obligatory, a high level of commitment is expected from senior management, supervisors and construction workers. Another strength of the study is the extensive evaluation in terms of both effect and process evaluation. The effect evaluation will include personal exposure assessment, as well as behavioral and organizational outcomes, which could provide meaningful results at worker, company and policy level (e.g., guidelines). A thorough process evaluation alongside a cluster RCT will provide more detailed information regarding the context and degree of the implementation of the intervention

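### As worded, the managers' control-measure session is open to both arms before follow-up, although the control group is to receive no intervention

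*Protocol article*

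**What the plan says.** The protocol article mentions a managers' session on technical control measures in several places.

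- Step 5 (plan for implementation): "Managers are also invited for a session with all participating companies to share ideas and learn about new innovations of technical control measures".
- Abstract, Methods/Design: "a demonstration session regarding control measures was organized for all managers".
- Discussion: "An additional informative session is therefore organized for all managers".
- Intervention program and materials, on the managers' separate meeting: "This meeting consists of a demonstration of the newest available technical control measures, their innovations and their possibilities". It is held at the same time as the worksite visits, in the research institute's laboratory, where managers can try the equipment.
- Table 2 lists among the intervention tools: "Tailored sessions for managers to demonstrate technical control measures".

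On the arms, the Study design section gives the intervention group the six-month programme, "while those allocated to the control group receive no intervention". The Randomization and blinding section gives as its first reason for randomising companies: "In order to avoid intervention group contamination". The Co-interventions section adds that managers were asked not to start other activities to lower quartz exposure during the intervention period.

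**The concern.** The session belongs to the intervention. It is described under the programme heading, listed in Table 2, and serves at least two of the managers' performance objectives in Table 1: knowing more about quartz exposure and supplying control measures to workers. The needs assessment makes companies responsible for having control measures on site. The Discussion gives the managers' role in that availability as the reason for the session.

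If control managers attend before T1, control worksites may change in the direction the trial is meant to test. The contrast in respirable dust and quartz would then be diluted, as would the contrasts in two secondary outcomes: the managers' organisational questionnaire and the observed use of control measures. The analysis could not remove this bias, because it would be part of what the control arm received.

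**Working it through.** **1. Who is invited.** Three places describe the audience (abstract, Step 5, Discussion), and none names an arm. The article can name one when it wants to: the Program description addresses the opening letter to workers in the intervention group.

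**2. What the phrase means elsewhere.** The trial has eight companies over both arms. Under Organizational factors, the outcome questionnaire is introduced with "Managers of all participating companies receive a questionnaire". That must cover both arms, because the outcome is compared between them. Step 1 also calls the study's companies participating, without reference to arm. The ordinary reading of Step 5 is therefore all eight.

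**3. When it happens.** The demonstration meeting runs alongside the worksite visits, so it falls within the six-month programme and before T1. Step 5 gives no date for its session. That the two are the same is an inference from the shared audience and subject (new control measures and their innovations).

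**4. The conflict.** Steps 1 to 3 taken literally invite control managers to an intervention component before T1. The Study design section gives the control group none.

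**5. The plan's own sample size.** The point does not rest on it. The article states 42 workers for a 30% change (alpha 0.05, 80% power), and 60 per group after a control-group decline and 20% loss. It gives no standard deviation, so 42 cannot be reproduced independently. Taking 42 as per arm, with a two-sided test on the log scale, the implied SD is 0.357 × √(42/2) / 2.802 = 0.583. With an assumed 2% control decline this gives 48 per arm, and 48 / 0.8 = 60. The stated figure is attainable under those assumptions.

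**6. Illustration of spill-over.** The documents give no spill-over size. Let control companies gain a share f of the planned log effect, δ = −ln(0.70) = 0.357. Then:

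- apparent reduction = 1 − 0.70^(1−f)
- power ≈ Φ(2.802 × (1−f) − 1.960), where 2.802 = 1.960 + 0.842 corresponds to 80% power at two-sided 0.05

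| Assumed f | Apparent reduction | 2.802 × (1−f) | Power |
|---|---|---|---|
| 0 | 30% | 2.80 | 80% |
| 0.10 | 27% | 2.52 | 71% |
| 0.25 | 23% | 2.10 | 56% |
| 0.50 | 16% | 1.40 | 29% |

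Starting instead from 48 evaluable workers per arm with SD 0.583 and no control decline, power is 85%, 77%, 61% and 32%. Both sets ignore clustering by company.

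**The case against.** The strongest reply is that Step 5 and the programme description belong to Phase I, which describes the intervention itself. There, a session with all participating companies can mean all companies taking part in the intervention, held jointly, in contrast to plenary sessions held within each company. Other components also lack an arm qualifier: the first plenary session is for all employees at the company, yet nobody would read that as covering controls. The questionnaire sentence concerns outcome measurement, where both arms must be included, so it does not settle the scope of a phrase in an implementation section. The Study design statement, as the governing one, could be taken to override the rest.

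Much of this stands. The authors may well have meant intervention companies only. Managers are invited, which is weaker than receiving, and the Study design sentence is worded for workers. The identity of the Step 5 session with the laboratory meeting is not stated.

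It does not remove the problem. The plenary sessions are tied to a single company, whereas the managers' session is expressly across companies, so here the missing qualifier matters. Managers are a declared target of the intervention, so a control arm free of intervention should exclude them too. No section supplies the restriction.

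A reader might go further and infer that control companies did receive part of the intervention, or that the trial's power is in fact 56% or 29%. The documents support neither: they record no attendance by control managers and give no spill-over size. The session is also only one element beside plenary meetings, worksite visits, factsheets, posters and letters, so a small share is as arguable as a large one.

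**Conclusion.** The wording is inconsistent on a matter that affects the between-arm contrast. Followed literally, the abstract, Step 5 and the Discussion invite control-company managers to an intervention component. If the session is the one held alongside the worksite visits, that is before T1. This conflicts with the no-intervention control group and with the reason given for randomising companies.

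This is an ambiguity to resolve, not an established design flaw. If control managers did attend before T1 and acted on it, the bias would be toward no effect. Its size is unknown. The 10% to 50% shares are assumptions, and the resulting figures also assume a two-sided test, a log-scale effect and no clustering.

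**What to change.** Reconcile the abstract, the Intervention program and materials section, Step 5, the Study design section and the Discussion. State that the session is for managers of intervention companies only until T1 measurements are complete in all companies. State also whether the Step 5 session and the laboratory demonstration are the same event, and when it takes place. The session may be offered to control companies after that.

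The abstract describes the session in the past tense, so it may already have been held. If control managers attended, record attendance by arm and report it as contamination that would bias the effect toward the null. The context element of the process evaluation can hold this record.

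The cost is a few words and an invitation list. A later session for control managers is optional. Sample size and analysis do not change.

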## Phase II: Evaluation of the intervention

### Step 6: Evaluation plan

#### Study design

The effectiveness of the intervention will be measured by performing a cluster randomized controlled trial (cluster RCT). Participants who have given informed consent are measured at baseline (T0), and will be measured after the intervention (T1). Workers at the worksite allocated to the intervention group receive the worksite intervention program during a six month period, while those allocated to the control group receive no intervention. The study protocol and measurements are not part of the judgement of the Central Committee of Research Involving Human Subjects, meaning no medical ethic approval is required for this study. The study has been executed according to the Dutch Data Protection Law.

#### Study population

The study population includes blue collar workers in the construction industry. These workers are recruited through eight companies specialized in either demolishing, concrete drilling, sawing and/or façade maintenance, which are all activities associated with relatively high silica exposure levels. Inclusion criteria for the construction workers are (i) available for the intervention period; (ii) sufficient competency in the Dutch language; and (iii) having signed a written informed consent to participate.

#### Recruitment of the study population

Companies were recruited via a request by sector organizations, either by distributing e-mails, hard copy invitations, or by telephonic contact. Within the company, support is needed at the level of manager, supervisor and worker
[31]. Therefore, at the start of the project, the senior management of the eight companies committed themselves to the project by signing a letter of intent. Additionally, they agreed that their workers (supervisors and blue collar workers) are allowed to participate in the program during working hours. The recruitment of workers was conducted by the principal researcher through the usual and available communication channels within the companies, e.g., intranet, a personal letter or verbally. Finally, the principal researcher ([name]) informed all workers at the worksites regarding study and distributed a letter with the content of the study.

#### Randomization and blinding

In order to avoid intervention group contamination, to obtain maximal co-operation of managers and construction workers, and to enhance participants' compliance, cluster randomization at the level of the company is considered the best randomization strategy for this study. Randomization is performed by the principal researcher ([name]) using an electronic randomization tool (
http://www.randomizer.org) after the baseline measurement. Because the intervention takes place at the worksites, participating workers, managers, supervisors, as well as researchers/trainers cannot be blinded to the group assignment.

#### Sample size

The sample size was calculated as the number of workers needed to identify an effect of the intervention on occupational exposure to quartz. A previous intervention study on occupational exposure to wood dust aimed to decrease the exposure by 30%
[34]. Assuming alpha is 0.05 and a power of 80% with a possibility to detect at least a 30% change in exposure in our intervention group, a sample size of 42 workers is needed. Although no specific information about exposure trends exists, it is well known that most occupational exposures show long-term downward trends of a few percent annually over recent decades
[35]. Assuming this is also the case for the Dutch construction industry, a decline in exposure in the control group over the course of this study was taken into account. Based on these calculations, and taking into account a loss-to-follow-up of 20%, it was estimated that 60 construction workers are necessary in both the intervention and control group.

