### Step 1: Needs assessment

In step 1 of the intervention mapping approach, insight into the underlying factors causing elevated levels of occupational quartz exposure was gained. Ultimately, this insight resulted in the formulation of the program objective. This objective specifies what changes are needed to decrease the elevated quartz exposure level.

Insight into the underlying factors was achieved by means of (i) a questionnaire and an exposure assessment survey among construction workers; (ii) a questionnaire among managers; (iii) a literature review; and (iv) meetings with managers and sector organizations in the construction industry.

The main resource for step 1 was an assessment of the baseline characteristics of the study population. This assessment focused on the role of behavioral and organizational factors in relation to quartz exposure among construction workers
[22]. The questionnaire distributed among construction workers was completed by 116 eligible participants, and produced insights in the behavioral factors. To explore the role of organizational factors, eight managers completed a questionnaire to obtain insight into the occupational safety and health policy of a company, using an adapted version from the Occupational Health and Safety Series (OHSAS) norm on hazardous circumstances
[23]. Additionally, a literature search was conducted in Pubmed, using keywords relevant for the target population (e.g., “construction workers”, “construction industry”, “concrete driller” and “demolisher”) and outcome measures (e.g., “occupational exposure”, “quartz”, and “silica”). Furthermore, two focus groups were organized: one group with seven researchers and one focus group with three managers and three representatives of sector organizations. Three additional face-to-face interviews with managers of participating construction companies were also organized.

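### The 80% power and 60 workers per arm rest on worker-level inputs only, although eight companies are randomised; the stated power is too high for any positive between-company correlation

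*Protocol article*

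**What the plan says.** The Sample size section of the protocol article takes the worker as its unit. The starting point is an alpha of 0.05 and "a power of 80% with a possibility to detect at least a 30% change in exposure in our intervention group", from which "a sample size of 42 workers is needed". Two adjustments follow: a downward trend in the control group, described only as a few percent a year, and 20% loss to follow-up. The result is that "it was estimated that 60 construction workers are necessary in both the intervention and control group". No ICC, design effect, company size, number of companies or standard deviation appears.

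Elsewhere the design is a cluster design. Under Study population, "These workers are recruited through eight companies". Under Randomization and blinding, "cluster randomization at the level of the company is considered the best randomization strategy for this study". Under Effect evaluation, the analysis is multi-level, with time, worker and company as the levels.

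**The concern.** The planned analysis carries between-company variance that the sample size leaves out. Workers in one company share management, equipment and type of work. The Study population section says the companies specialise in different activities, and the Needs assessment makes the availability of control measures a company responsibility. A positive ICC for exposure is therefore plausible.

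The power claim concerns the primary outcome. If it stands uncorrected, a non-significant result may be given more weight as evidence against a 30% reduction than the design can bear. The Discussion expects the findings to play a part in employers' investment decisions.

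**Working it through.** **Inputs from the article:** alpha 0.05 (two-sided assumed), power 80%, 30% change, 42 workers, 20% loss, 60 per arm, eight companies. **Assumptions:** 42 is per arm; four companies per arm of equal size; analysis on the log scale; ICC over a range.

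**1. Can the 42 be reproduced?** Not directly, because no standard deviation is given. It can be back-solved. The log effect is −ln(0.70) = 0.357. From n = 2·SD²·(1.960 + 0.842)²/0.357² with n = 42, SD = 0.583 on the log scale.

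**2. Do the named adjustments account for the 60?** Completers per arm are 60 × 0.80 = 48. Moving from 42 to 48 means that the net log effect falls to 0.357 × √(42/48) = 0.334, a net reduction of 1 − exp(−0.334) = 28.4%. The control decline that produces this is 1 − 0.70 × exp(0.334) = 2.3%, which fits a few percent. By contrast, 42/0.80 = 52.5, so loss alone does not give 60. On this reading the two named adjustments use up the whole increase, and no room remains for an unstated design effect. If 42 were a total (21 per arm), the decline would have to be about 11%, which does not fit. No cluster allowance is named on either reading.

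**3. Power with company as the unit of randomisation.** With m = 48/4 = 12 completers per company, the design effect is DE = 1 + 11 × ICC. At DE = 1 the standard error is 0.583 × √(2/48) = 0.119, and 0.334/0.119 gives the ratio 2.80 that corresponds to 80% power. Clustering divides this ratio by √DE. Normal-approximation power is Φ(2.80/√DE − 1.96). The t version uses the non-central t on 8 − 2 = 6 degrees of freedom (critical value 2.447).

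| ICC | DE | Effective n per arm | Power, normal | Power, t on 6 df |
|---|---|---|---|---|
| 0 | 1.00 | 48 | 80% | 65% |
| 0.01 | 1.11 | 43 | 76% | 60% |
| 0.02 | 1.22 | 39 | 72% | 57% |
| 0.05 | 1.55 | 31 | 61% | 47% |
| 0.10 | 2.10 | 23 | 49% | 37% |
| 0.20 | 3.20 | 15 | 35% | 26% |

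**4. Detectable reduction at 80% power.** This is 1 − exp(−c × 0.119 × √DE), with c = 2.80 for the normal approximation and c = 3.37 for t on 6 df.

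| ICC | Normal | t on 6 df |
|---|---|---|
| 0 | 28% | 33% |
| 0.05 | 34% | 39% |
| 0.10 | 38% | 44% |

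The two columns should not be mixed. On either test an ICC of 0.05 costs about 6 percentage points.

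**5. If the target is a full 30% between-arm difference** on the same SD, normal-approximation power at 48 per arm is 85% at ICC 0, 81% at 0.01, 77% at 0.02, 67% at 0.05 and 54% at 0.10.

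**The case against.** The strongest reply is that nearly every quantity above is back-solved or assumed. The SD and the 2.3% decline are fitted, the ICC is not in the article, and no arithmetic slip is shown. That is fair as to size. It does not touch the direction, which follows from the design effect exceeding 1 whenever the ICC is positive.

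The multi-level analysis already accounts for clustering. This is true, and it means that the omission affects the power statement, not the planned treatment of clustering in the effect estimate. Adjustment for job category and use of the repeated measurements may also recover some precision, but the Sample size section does not claim that as an offset.

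The 6 df figures presuppose a company-level test, whereas the article names no method for degrees of freedom. They are therefore conditional, and the normal-approximation figures are given beside them.

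A reader might infer three stronger things that the article does not support:

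- **That the trial would probably miss a true 30% effect.** By the normal approximation, power for the net effect falls below 50% only from an ICC of about 0.10, and for a full 30% difference it is still 54% there. The ICC is unknown.
- **That more workers per company would hardly help.** Going from 12 to 24 completers per company raises normal-approximation power from 76% to 95% at ICC 0.01 and from 61% to 77% at 0.05. Only from about ICC 4/48 = 0.083 can no number of workers in eight companies restore 80%.
- **That 42 is a one-sample before-after number,** because the 30% is described for the intervention group. On that reading, power for a 30% between-arm difference at 48 per arm would be 56% before clustering. But the section also allows for a control-group decline and sizes both arms, so a between-arm contrast is evidently in view.

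**Conclusion.** The point holds as an omission in the sample-size reasoning. The article itself lists the steps from 42 to 60, so this is not a detail left to a fuller document. For the effect the trial was sized on, power is below the stated 80% at any positive ICC, and testing on few degrees of freedom lowers it further.

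The size can only be given as a range. Between ICC 0.01 and 0.10, power is about 76% down to 49% by the normal approximation, or about 60% down to 37% on 6 df. This rests on a 4 v 4 split, 12 completers per company, equal company sizes and the back-solved SD. Unequal company sizes would lower power further. The article does not establish where in the range the trial lies.

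**What to change.** Leave enrolment and analysis as they are and rewrite the power statement in the Sample size section:

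- Replace the 80% claim with the power for a 30% between-arm difference, and the between-arm reduction detectable at 80% power, for eight companies. Use the design effect 1 + (m − 1) × ICC and small-sample degrees of freedom.
- Give both over a range of ICCs, not as one figure. The baseline data can inform the range: the baseline survey is done, and its worker questionnaire "was completed by 116 eligible participants", or 116/8 = 14.5 per company. Use the company variance after adjustment for job category, since a raw baseline ICC would include differences in type of work that the planned model adjusts for. Note that eight companies estimate it imprecisely.
- State the SD, and whether 42 is per arm or in total.
- State that a non-significant result does not exclude a 30% reduction.

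The cost is one paragraph and a short calculation. The stated power becomes less favourable.
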